### Controlled ovarian hyperstimulation

A short protocol will be suggested to all patients. On cycle day 2, gonadotropin-releasing hormone (GnRH) agonist (Triptorelin; Tiantai Mountain Pharmaceutical Company, Chengdu, China) 0.05~0.1 mg will be initiated. From cycle day 4, all patients will be stimulated with gonadotrophin (Gn) (FSH/human menopausal gonadotrophin; Livon, Zhuhai, China) 150 or 225 IU/day. Both GnRH agonist and Gn continue until the day of human chorionic gonadotropin (hCG) administration. On stimulation day 6, transvaginal ultrasound scans and serum hormone tests will be performed. The dose of Gn will be adjusted according to follicular development and endocrinometry. Afterward, such monitoring will be performed every other day or every day. When more than two lead follicles reach at least 18 mm, 6000–10,000 IU of hCG will be administered to trigger final follicular maturation.

### Oocyte retrieval, in vitro fertilization, and embryo culture

Transvaginal ultrasound-guided ovum pickup takes place about 34–36 h after hCG administration. Oocytes will be inseminated by IVF or ICSI according to the quality of sperm. Embryo transfer (ET) is routinely performed on days 3 after fertilization at the cleavage stage, and a maximum of two top quality embryos will be transferred through a catheter by using transabdominal ultrasound guidance (full bladder). If the quality of the embryo is poor, ET will be performed on day 2 or 5. Blastocyst culture and vitrification will be performed for the surplus embryos. All of the operations will be performed by experienced clinicians.

### Luteal phase support

Dydrogesterone tablet (Duphaston, Abbott, Hoofddorp, The Netherlands) 20 mg twice daily orally or vaginal progesterone gel (Crinone gel, 8%, Merck Serono, Geneva, Switzerland) 90 mg once daily will be used for luteal phase support (LPS) from the day after oocyte retrieval for 2 weeks. After a positive pregnancy test (serum β-hCG ≥10 IU/L), LPS will be continued until at least 10 weeks’ gestation. If β-hCG is negative or if the pregnancy fails, LPS will be stopped. If a biochemical pregnancy has been achieved, ultrasound scan will be performed at 5–6 weeks after ET to assess clinical pregnancy and repeated at 12 weeks’ gestation to confirm ongoing pregnancy.

#### Outcome measurement

##### Primary outcome

The primary endpoint of study is live birth, defined as delivery of any neonate at at least 28 weeks’ gestation with signs of life after ET.

##### Secondary outcomes

Secondary outcomes will include (1) change of ovarian reserve index (basal serum FSH, anti-Müllerian hormone (AMH), and antral follicle counts), (2) indexes of ovarian response (total gonadotropin dosage, estradiol (E2) on the HCG trigger day, and retrieved oocyte number), (3) indicators of oocytes quality (mature oocyte rate, normal fertilization rate, and number of top-quality embryos), and (4) CPR and miscarriage rate.

Biochemical pregnancy is defined as a serum β-hCG level of at least 10 IU/L 2 weeks after ET. Clinical pregnancy is defined as detection of intrauterine gestation sac after 3 weeks after a biochemical pregnancy is confirmed. Ongoing pregnancy is defined as detection of a viable fetus with fetal heartbeat at 11–12 weeks’ gestation. Cumulative live birth will be defined as each woman having only one allowable live birth from the single IVF cycle.

##### Follow-up protocol

First pregnancy follow-up time point is at 12 weeks’ gestation when the participants come for their clinic visits. The presence of first-trimester pregnancy complications (Ovarian hyperstimulation syndrome (OHSS), miscarriage, ectopic pregnancy, or gestational trophoblastic disease or a combination of these) will be evaluated by inspecting medical records and be recorded by completing the case report form. Moderate OHSS is diagnosed when ultrasonographic ascites is present in addition to abdominal distension and discomfort with or without nausea, vomiting, or diarrhea or a combination of these. Severe OHSS is diagnosed when there is clinical evidence of ascites and/or hydrothorax or breathing difficulties with or without hemoconcentration, coagulation abnormalities, and diminished renal function.

Second pregnancy follow-up time point is at 28 weeks’ gestation. The second-trimester pregnancy complications (prenatal diagnosis test results, abortion, gestational diabetes, preeclampsia/eclampsia, incompetent cervix, premature rupture of membrane, or placenta abruption or a combination of these) will be followed up by telephone call.

Third pregnancy follow-up time point is at 37 weeks’ gestation. The third-trimester pregnancy complications (preterm labor, placenta abruptio, placenta accreta, placenta previa, preeclampsia/eclampisa, intrauterine growth retardation, premature rupture of membrane, or abnormality of amniotic fluid or a combination of these) will be followed up by telephone call.

Fourth follow-up time point is at delivery. Participants will be required to inform investigators of the delivery time. The obstetrical and perinatal complications (gestational age, delivery mode, placenta abnormality, or delivery complications or a combination of these) as well as neonatal information (gender, birth weight, and birth defect) will be obtained and recorded to complete designed forms. If possible, copies of the obstetric medical records will be performed for the study chart source documents.

The fifth and final follow-up time point is at 6 weeks after delivery. Postpartum complications (postpartum depression, infection, and late postpartum hemorrhage) and neonatal complications (neonatal respiratory distress syndrome, neonatal jaundice, neonatal infection, neonatal death, and neonatal hospitalization) are followed up by telephone call.

##### Adverse events

Adverse events are defined as any untoward or unfavorable medical occurrences associated with the subject’s participation during the research regardless of whether they are considered related to the study intervention. Serious adverse events are defined as events that are temporally associated with the subject’s participation in research: death, life-threatening or severely or permanently disabling events, events requiring in-patient hospitalization or prolongation of existing hospitalization, pregnancy loss after 20 weeks’ gestation, neonatal death up to 6 weeks after delivery, congenital anomaly or birth defect, or any events deemed serious by the local principal investigator.

All of the adverse events will be recorded in detail. Serious adverse events will be reported to the principal investigator immediately, and appropriate measures will be initiated instantly. The ethics committee will determine whether the adverse event is likely to have been associated with the experimental drug and whether it is necessary to break blinding codes.

### Data management

All data will be collected with a standard case report form developed in the web-based data entry system by the double-entry method. Before being input into the database, data will be de-identified. Paper files will be kept in a locked filing cabinet in the treating hospital. Electronic documents will be stored in a password-protected computer, and access will be restricted to the principal investigator. The study site monitor of Shandong University will check the authenticity, accuracy, and integrity of the data regularly to ensure the accuracy of collected data. The data will be stored for at least 5 years after publication.

All data will be supervised by independent statisticians from Shandong University. The clinical research must be carried out under the rules on China’s New Drug Examination and Approval and Management Standard of the Clinical Test of Drugs (Good Clinical Practice). Data monitors will check and review the quality of data collected in the research accordingly.

#### Data analysis plan

Statistical analysis will be performed by using Statistical Package for the Social Sciences Version 22.0 (SPSS Inc., Chicago, IL, USA). Normally distributed continuous variables are expressed as mean ± standard deviation with a Wilcoxon rank-sum test for testing between-group differences. Non-normally distributed continuous variables are expressed as medians and ranges, and categorical data are described as frequency, percentage, and constituent ratio.

The primary analysis will use an intention-to-treat analysis approach to examine differences in the live birth rate between the two treatment arms by the Pearson chi-squared test. Secondary efficacy parameters and safety parameters (pregnancy rate, OHSS rate, and so on) will be analyzed by using the Pearson chi-squared test. The Wilcoxon rank-sum test will be performed to compare continuous parameters (retrieved oocyte number, gonadotropin dosage, E2 level on the hCG trigger day, and so on). The analysis of covariance (ANCOVA) tests will be used to compare the indicators (basic FSH, E2 level, and AMH level) pre- and post-treatment between-group, and pre-post paired *t* tests will be used within-group.

A secondary per-protocol analysis will be performed according to the actual treatment that subjects received.

Results will be presented as point estimates and 95% confidence intervals; the level of significance will be set at 5%.

The flowchart of this study is presented in Fig. 1, and the SPIRIT checklist is included as Fig. 2.

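### Rank-sum tests are paired with normal data shown as means, and within-arm pre-post t tests are planned where only the between-arm comparison is randomised (minor; secondary outcomes only)

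*Protocol article*

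**What the plan says.** All the test rules stand in the Data analysis plan of the protocol article.

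- For normal variables: "Normally distributed continuous variables are expressed as mean ± standard deviation with a Wilcoxon rank-sum test for testing between-group differences".
- For the others: "Non-normally distributed continuous variables are expressed as medians and ranges". That sentence names no test.
- A later sentence is general: "The Wilcoxon rank-sum test will be performed to compare continuous parameters". Its examples are oocyte number, gonadotropin dose and trigger-day E2, and the list is open-ended.
- For hormones measured before and after treatment: "The analysis of covariance (ANCOVA) tests will be used to compare the indicators (basic FSH, E2 level, and AMH level) pre- and post-treatment between-group". The sentence then adds that "pre-post paired *t* tests will be used within-group".
- For reporting: "Results will be presented as point estimates and 95% confidence intervals", at a 5% significance level.

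The Secondary outcomes section lists first the "change of ovarian reserve index", made up of basal FSH, AMH and antral follicle count. The primary analysis is an intention-to-treat Pearson chi-squared test on live birth.

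**The concern.** There are two separate faults, and both lie in rules the article states, not in detail it leaves out.

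**Test and estimate do not match.** For a normally distributed variable the reader will see two means, presumably their difference with a 95% interval, and a p-value. The p-value comes from a rank-sum test, which addresses whether values in one arm tend to exceed those in the other. It is not a test of the mean difference and produces no interval for it, so the interval and the p-value can fall on opposite sides of the 5% line. The non-normal variables, for which a rank-sum test is the usual partner, have no test in their own sentence. That suggests a clause was lost.

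**Within-arm tests are not randomised comparisons.** A paired t test inside the DHEA arm asks whether a marker changed over 4–12 weeks. It cannot separate the drug from time, cycle-to-cycle variation or regression to the mean. A significant change on DHEA beside a non-significant one on placebo reads as a drug effect, yet the two arms have not been compared. The Background criticises earlier evidence as mostly retrospective or observational. Within-arm p-values would bring uncontrolled inference back into a placebo-controlled trial.

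**Working it through.** **The plan's own figure.** The only sample-size figure concerns live birth: 20% versus 30%, 80% power, 5% level (taken as two-sided, and the difference of 10 as percentage points). With the pooled-variance formula, n = [1.960·√(2·0.25·0.75) + 0.842·√(0.2·0.8 + 0.3·0.7)]² / 0.10² = (1.200 + 0.512)² / 0.01 ≈ 293.2, so 294 per arm. The stated figure reproduces, with power 80.1%. The article gives no figure for continuous outcomes, so what follows rests on assumptions.

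**Inputs.** From the article: 355 enrolled per arm and 20% dropout, so 355 × 0.8 = 284 analysable per arm. Assumed: pre-post correlation 0.7, and a common shift of 0.05 to 0.20 SD in both arms with no drug effect.

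**Rank-sum on normal data.** The large-sample efficiency of the rank-sum test relative to the t test on normal data is 3/π = 0.955, equivalent to 284 × 0.955 ≈ 271 per arm. At a true difference of 0.236 SD, 4,000 simulated trials give power of 80.3% (t test) and 78.8% (rank-sum). With no difference, rejection is 5.5% and 5.3%. Validity is intact and the power cost is small; what remains is the mismatch between p-value and estimate.

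**Within-arm paired t test, no drug effect.** In SD units the pre-post difference has standard deviation √(2·(1 − 0.7)) = 0.775. The noncentrality is shift × √284 / 0.775. With p the rejection probability in one arm, exactly one arm is significant with probability 2p(1 − p).

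| Common shift (SD) | Noncentrality | Active arm significant: formula | Active arm significant: simulation | Exactly one arm significant: formula | Exactly one arm significant: simulation | Between-arm ANCOVA rejects: simulation |
|---|---|---|---|---|---|---|
| 0.05 | 1.09 | 19% | 19% | 31% | 31% | 5% |
| 0.10 | 2.18 | 58% | 57% | 49% | 50% | 5% |
| 0.15 | 3.26 | 90% | 90% | 18% | 18% | 5% |
| 0.20 | 4.35 | 99% | 99% | 2% | 2% | 5% |

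Worked row at 0.10 SD: 0.10 × 16.85 / 0.775 = 2.18, so p ≈ 0.58, and 2 × 0.583 × 0.417 ≈ 0.49. The simulations used 4,000 trials per row; a repeat gave 18% at the smallest shift.

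The paired test does its own job correctly, since a shift did occur. The error lies in reading that shift as an effect of DHEA. The between-arm ANCOVA cancels the common shift and keeps its nominal level.

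**The case against.** **The valid comparison is already planned.** The between-arm ANCOVA and the paired tests share one sentence, and nothing says efficacy will be concluded from the within-arm p-values. This stands and limits the harm. It does not make the within-arm tests useful, because they add p-values that answer no randomised question.

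**The rank-sum pairing looks like a drafting slip, and the test is valid on normal data.** Both are true. Under a pure shift model a Hodges–Lehmann interval would even estimate the same shift as the mean difference. But the article pairs the test with means and standard deviations, and as written the rule would be followed.

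**A reader might infer that a false within-arm improvement is nearly certain because poor responders were selected.** The documents do not support this. Simulated rejection is very high (84–100%, for entry on the lower 20–50% of the tested marker with reliability 0.7–0.9) only if the qualifying reading also serves as baseline. With a separate baseline reading it falls to about 4–5%. The Intervention section places recruitment before baseline assessment, which allows a separate reading. The article also does not set out which markers drive entry under the Bologna consensus.

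**A reader might infer that ANCOVA is the wrong method for the hormones because they are skewed.** The article states neither skewness nor an untransformed scale, and the scale of analysis may be left to a fuller document. Even on simulated lognormal data, raw-scale ANCOVA kept its type I error at 4.8–5.2%. The possible cost is power, and it depends on an assumed spread. For a true 15% rise, raw versus log power is 99% versus 100% at log-SD 0.5, 63% versus 82% at 0.8, and 37% versus 65% at 1.0.

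**Antral follicle count is not left without a test.** It is absent from the ANCOVA list, but the open-ended rank-sum rule can cover it. Using the baseline-adjusted model would be consistent with FSH and AMH; its absence is not an error.

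**Conclusion.** The point holds in a limited form and is minor. Two stated rules should change: the rank-sum test attached to normal variables shown as means, and the within-arm paired t tests. The first costs about 1–2 points of power and leaves p-values that do not match the estimates. The second can produce significant within-arm changes with no drug effect in about 18–99% of trials. That range depends entirely on the assumed common shift and on the assumed 284 per arm and correlation of 0.7. If there is no shift at all, the rate is the nominal 5%. It would be wrong to conclude that the trial will report improvement whatever DHEA does: the size of any common shift is unknown, and a sound between-arm analysis is in the plan. Every affected outcome is secondary. The primary chi-squared analysis and the sample size are not touched.

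**What to change.** In the Data analysis plan:

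1. Drop the within-arm paired t tests. Show change within each arm descriptively, without p-values.
2. State that every ovarian-reserve conclusion rests on the between-arm ANCOVA with the baseline value as covariate, and add antral follicle count to that list.
3. For approximately normal variables, use a t test or linear model and report the mean difference with its 95% interval.
4. For skewed variables, keep the rank-sum test and report a Hodges–Lehmann estimate with its 95% interval. Reword the general rank-sum sentence to agree.
5. Optionally, allow log-scale analysis of the hormones if skew is observed, with the criterion fixed before unblinding.

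The cost is analysis wording only: no extra participants, visits or data. The Trial status section reports enrolment still under way, and allocation stays blinded to the end of the study, so the change could be made before unblinding.

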### Study sites

This clinical trial involves eight hospitals in China. Live birth rate of active group versus placebo group will be compared in a pool of 710 infertile POR patients undergoing their sequence cycle of IVF/ICSI. The study will be conducted in accordance with Good Clinical Practice guidelines and the Declaration of Helsinki. The study has been approved by the ethics committees at all hospitals and facilities.

The trial and study plan will be declared to all participants at their first visit. If patients are eligible and interested in participating, the couples will be asked to sign an informed consent form giving permission to use their results anonymously in future studies. Reporting of the study results will follow the 2010 revised CONSORT (Consolidated Standards of Reporting Trials) statement [23]. An overview of specific measurements and time points of data collection can be found in the SPIRIT (Standard Protocol Items: Recommendations for Interventional Trials) Figure (Fig. 2, Additional file 1).

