### Determination of the sample size

The sample size calculation is based on the live birth rate. Data from our hospital indicated that the live birth rate of infertile POR undergoing IVF/ICSI cycles was 20%. In our present study, we plan to test the primary hypothesis of a difference of 10 in the live birth rate for the two randomization arms. A sample size of 294 prospectively enrolled participants in each randomization arm will yield a statistical power of 80 at a *P* value of less than 0.05 to demonstrate a significant difference in live birth rates of 10 between treatment arms. In consideration of a dropout rate of 20%, we will enroll 355 participants each group.

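### The primary live-birth test is valid but unadjusted, so it forgoes a modest, assumption-dependent gain in power from baseline data the trial already collects

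*Protocol article*

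**What the plan says.** The Data analysis plan of the protocol article sets the primary analysis by intention to treat, examining "differences in the live birth rate between the two treatment arms by the Pearson chi-squared test". It names no covariate, no centre term and no adjusted supporting analysis for live birth. It also states "Results will be presented as point estimates and 95% confidence intervals". ANCOVA is planned for FSH, E2 and AMH.

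Under Secondary outcomes, the first item is "change of ovarian reserve index", made up of basal FSH, AMH and antral follicle count. A change needs a baseline value, so these measurements will exist. Age is not listed as a collected variable but will be known for every participant. Under Study sites: "This clinical trial involves eight hospitals in China".

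The section on sample size assumes "live birth rate of infertile POR undergoing IVF/ICSI cycles was 20" per cent and a "difference of 10 in the live birth rate for the two randomization arms". It says that 294 per arm "will yield a statistical power of 80" per cent, and enrols 355 per arm to allow for 20% dropout.

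**The concern.** When a baseline variable predicts a binary outcome, a comparison that conditions on it has more power than one that does not, at the same sample size. The trial has such candidates to hand and leaves them out of the analysis that decides it. The Background links IVF outcome to oocyte yield, above all in women with poor response or advanced age, so it is reasonable to expect age and ovarian reserve to carry some prognostic information.

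At stake is power near the planned 80%. If 20% of the 355 per arm are lost and excluded, 355 x 0.8 = 284 remain, slightly fewer than the 294 required. Extra precision without extra participants would be useful there. An analysis restricted to arm alone is a stated choice of primary method, not a detail left to a statistical analysis plan.

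**Working it through.** **Inputs from the article.** Control rate 20%; difference 10, read as percentage points upward (20% vs 30%); power 80%; significance level 5%, read as two-sided; 294 per arm required and 355 enrolled; eight hospitals. **Assumed, because the article gives no figure:** the share of outcome variance explained by the baseline covariates, R-squared 0.02 to 0.15.

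**1. The plan's own figure.** With pooled variance under the null and mean rate 0.25:

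n = [1.960 x sqrt(2 x 0.25 x 0.75) + 0.842 x sqrt(0.2 x 0.8 + 0.3 x 0.7)]^2 / 0.10^2
= [1.960 x sqrt(0.375) + 0.842 x sqrt(0.37)]^2 / 0.01
= (1.2002 + 0.5119)^2 / 0.01 = 293.1, rounded up to **294**.

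This is an exact match, so the sample size was calculated for the plain two-proportion test that the plan uses.

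**2. Unadjusted power.** Power = Phi[(0.10 - 1.960 x SE0) / SE1], with SE0 = sqrt(0.375/n) and SE1 = sqrt(0.37/n). At n = 294: SE0 = 0.03571, SE1 = 0.03548, and Phi(0.846) = 80.1%. The same formula gives 78.7% at 284 and 87.0% at 355.

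**3. Adjusted power.** As an approximation, multiply both variances by (1 - R-squared). Example at n = 284 and R-squared 0.05: SE0 = sqrt(0.375 x 0.95/284) = 0.03542, SE1 = sqrt(0.37 x 0.95/284) = 0.03518, and Phi(0.869) = 80.8%.

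| n per arm | Unadjusted | R-squared 0.02 | 0.05 | 0.10 | 0.15 |
|---|---|---|---|---|---|
| 284 | 78.7% | 79.5% | 80.8% | 82.8% | 84.9% |
| 294 | 80.1% | 80.9% | 82.1% | 84.1% | 86.1% |
| 355 | 87.0% | 87.6% | 88.6% | 90.2% | 91.7% |

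An R-squared of about 0.05 is enough to bring 284 per arm back above 80%; 0.02 is not. Put another way, 294 x (1 - R-squared) gives 289, 280, 265 and 250 adjusted participants per arm with the power of 294 unadjusted.

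**4. Simulation check.** One normally distributed score, marginal rates held at 20% and 30%, 294 per arm, 3,000 trials per setting (Monte Carlo standard error about 0.7 points, from sqrt(0.8 x 0.2/3000)):

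| C-statistic of score | Implied R-squared | Chi-squared | Adjusted logistic |
|---|---|---|---|
| 0.50 | 0 | 80.0% | 79.9% |
| 0.61 | 0.025 | 80.4% | 81.8% |
| 0.66 | 0.054 | 81.1% | 83.8% |
| 0.71 | 0.092 | 81.3% | 84.4% |
| 0.75 | 0.134 | 80.1% | 85.5% |

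Gains run from 1.4 to 5.4 points, and a score with no prognostic value costs nothing material. The simulation used a single score. The proposed model has 1 arm term + 3 covariates + 7 centre terms = 11 terms, against 0.25 x 568 = 142 expected live births at 284 per arm. That is about 13 per term, which is workable, but the small cost of estimating the extra terms is not counted.

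**5. Type I error of the planned test.** Under no effect, with eight centres of unequal live birth rates, allocation not stratified by centre and 355 per arm, the chi-squared test rejected in 5.0% to 5.5% of simulated trials. It stays at about its nominal level.

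**The case against.** The strongest reply is that nothing here is wrong. A chi-squared test in the intention-to-treat set is a valid primary analysis of a binary outcome, holds its error rate, and is the test for which the trial was sized. That stands, and it limits the point to efficiency.

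The size of the gain is also open. The Background's link is with oocytes retrieved, which is measured after randomisation and gives no strength for age or reserve at baseline. Entry under the Bologna criteria may narrow ovarian reserve, so the gain may be below one point. And 284 per arm assumes that dropouts are excluded, whereas the analysis is by intention to treat: with all 355 analysed at 20% vs 30%, unadjusted power is already 87.0%. If dropouts count as no live birth (0.8 x 20% = 16% vs 0.8 x 30% = 24%), it is 76.1%. No adjusted figure was calculated for that case, where dropout unrelated to prognosis would also dilute what the covariates explain. All this stands as a caution on size, not on direction.

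The contrast with ANCOVA carries little weight: there the covariate is the baseline value of the outcome itself, and live birth has none.

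Three stronger readings are tempting, and the article supports none of them:
- **That the plan yields no effect estimate.** Estimates with 95% intervals are promised, and a risk difference or ratio follows from the same two-by-two table.
- **That randomisation is unstratified.** Randomization and blinding describes a centrally held list and is silent on strata. A condensed article may omit this.
- **That chance imbalance biases the test.** Random imbalance is already allowed for in the nominal error rate, as step 5 illustrates.

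**Conclusion.** The point holds as a missed gain in efficiency, not as an error. The primary test does not use pre-treatment AMH, antral follicle count, FSH or age, and an adjusted analysis would do better if these predict live birth. The gain is about 1 to 6 points of power at 284 to 294 per arm and about 1 to 5 points at 355.

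These figures rest on 20% vs 30%, a two-sided 5% level and an R-squared of 0.02 to 0.15 that the article neither gives nor excludes; the lower part of the range is plausible. The case for including centre is precision only, since the article describes no stratification factor that the analysis would be obliged to carry. An unseen analysis plan might add an adjusted supporting analysis, but the article fixes the primary one as unadjusted. The change is worth making because it is cheap and has little downside; the trial's conclusion would remain valid without it.

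**What to change.** Before unblinding, prespecify as the primary analysis an intention-to-treat logistic regression of live birth on arm, with pre-treatment age, AMH and antral follicle count, plus centre. Report it as a standardised (marginal) risk difference with a 95% confidence interval, which keeps the result on the scale of the sample size calculation. Retain the unadjusted Pearson chi-squared test as a supporting analysis.

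Use only covariate values measured before the first dose, because DHEA may change later ones and adjusting for those could remove part of the effect.

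Fix in advance the functional form of each covariate, how missing covariate values are handled, and what is done if a small centre has too few events for its own term.

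The cost is a change of analysis wording and some programming; the standardisation and its interval may need code beyond routine SPSS output. No participants or measurements are added. According to Trial status, enrolment was still under way at submission, and allocation stays blinded until the end of the study, so prespecification was still possible then.

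### The chi-squared rule for secondary rates makes no exception for the mature oocyte and normal fertilization rates, which have several oocytes per randomised woman

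*Protocol article*

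**What the plan says.** In the protocol article, Secondary outcomes lists three oocyte-quality indicators: "mature oocyte rate, normal fertilization rate, and number of top-quality embryos". The first two are proportions of oocytes. Neither a denominator nor a unit of analysis is given for them.

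The Data analysis plan then assigns tests by type of parameter:

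- Pearson: "Secondary efficacy parameters and safety parameters (pregnancy rate, OHSS rate, and so on) will be analyzed by using the Pearson chi-squared test".
- Wilcoxon: "The Wilcoxon rank-sum test will be performed to compare continuous parameters (retrieved oocyte number, gonadotropin dosage", followed by the estradiol level and an open end to the list.
- ANCOVA and paired t tests for the hormone measurements before and after treatment.

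It also promises point estimates with 95% confidence intervals, and "the level of significance will be set at 5" per cent. Randomization is by woman, 1:1. No method that allows for several oocytes per woman is named.

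**The concern.** The Pearson test compares counts of independent units. Pregnancy and OHSS, the two examples in the chi-squared sentence, meet that condition because each woman contributes one result. The two oocyte rates do not. They fit a two-by-two table only if all oocytes in an arm are pooled and each is counted as its own subject.

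Oocytes from one woman share her age, ovaries and stimulation, and for fertilization usually the same sperm. A positive correlation within the woman is therefore to be expected. The pooled variance then understates the true variance, so p-values are too small and intervals too narrow.

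At stake is whether a null effect of DHEA on oocyte quality could be reported as a finding more often than the stated 5%. Oocyte quality is a named group of secondary outcomes, and the Discussion presents the trial as a source of level I evidence.

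**Working it through.** **The plan's own figure.** The article calculates a sample size only for live birth. Its inputs are that "the live birth rate of infertile POR undergoing IVF/ICSI cycles was 20" per cent, and "we plan to test the primary hypothesis of a difference of 10 in the live birth rate for the two randomization arms", read as 20% against 30%. With two-sided 5% and 80% power, pooled variance and no continuity correction:

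n = [1.96 × √(2 × 0.25 × 0.75) + 0.8416 × √(0.2 × 0.8 + 0.3 × 0.7)]² / 0.1² = (1.2003 + 0.5119)² / 0.01 ≈ 293.2, so 294 per arm.

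This matches the article. Live birth is one result per woman, so the calculation has no clustering problem and says nothing about the oocyte rates.

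**Which test covers the oocyte rates.** Both examples in the chi-squared sentence are rates. The Wilcoxon examples are a count, a dose and a hormone level. The two oocyte quantities are called rates and are secondary efficacy outcomes, so the natural reading puts them under Pearson.

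**Size if oocytes are pooled.** The inputs below are assumptions, because the article gives none for this trial:

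- Mean oocytes per woman: 2 to 4. The Background mentions women with fewer than five oocytes, but that is a cited group.
- Within-woman correlation (ICC): 0 to 0.3.
- Counts: Poisson.

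When the number of oocytes m varies between women, the design effect is DE = 1 + (mean − 1 + variance/mean) × ICC. For Poisson counts the variance equals the mean, so DE = 1 + mean × ICC. The true error of a nominal 5% test is 2 × [1 − Φ(1.96/√DE)]. The last column is from simulated null trials with 355 women per arm, beta-binomial outcomes, a rate of 0.8 and 4000 runs per row.

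| Mean oocytes | ICC | DE | Error, formula | Error, simulated |
|---|---|---|---|---|
| 2 | 0.1 | 1.2 | 7.4% | 8.4% |
| 2 | 0.2 | 1.4 | 9.8% | 9.5% |
| 2 | 0.3 | 1.6 | 12.1% | 12.2% |
| 3 | 0.1 | 1.3 | 8.6% | 9.2% |
| 3 | 0.2 | 1.6 | 12.1% | 11.8% |
| 3 | 0.3 | 1.9 | 15.5% | 15.3% |
| 4 | 0.1 | 1.4 | 9.8% | 10.0% |
| 4 | 0.2 | 1.8 | 14.4% | 14.8% |
| 4 | 0.3 | 2.2 | 18.6% | 18.8% |

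Formula and simulation agree closely. The first row differs by about two simulation standard errors (√(0.084 × 0.916/4000) = 0.44 points), so the lower end is best read as 7% to 8%.

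- **ICC 0:** DE = 1 and nothing is inflated. The simulations gave 4.4% to 5.7%.
- **Overdispersed counts:** the error rises. With a variance of twice the mean, mean 4 and ICC 0.3, DE = 1 + (4 − 1 + 2) × 0.3 = 2.5 and the error is 2 × [1 − Φ(1.96/√2.5)] = 21.5%.
- **Interval width:** a naive interval has 1/√DE of its proper width. That is 1/√1.2 = 0.91 to 1/√2.2 = 0.67 over the table, so 9% to 33% too narrow.
- **Woman as the unit:** one proportion per woman with at least one oocyte, compared by Wilcoxon in the same simulated settings (1000 runs each), gave 3.9% to 5.3%.

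**The case against.** The strongest reply is that the article never says oocytes will be pooled. The chi-squared sentence does not name the oocyte rates, and its two examples are one per woman. It cannot literally cover every secondary efficacy parameter, because the next sentences send oocyte number, gonadotropin dose and hormone levels to other tests. A proportion calculated for each woman is a continuous variable and could fall under the open Wilcoxon list, where the error is held. The article is also a condensed text, and a fuller plan may settle the unit of analysis.

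Much of this stands. A reader might infer that the plan prescribes pooling of oocytes, or that 8% to 19% is a property of this trial. The article supports neither: the first is the natural reading but not the only one, and the second depends on assumed counts and correlation.

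A reader might also extend the point to "CPR and miscarriage rate", or to women without oocytes dropping out of the comparison. Clinical pregnancy and miscarriage are not oocyte-level outcomes, and the article does not state the denominators, so those are side issues. Nor does it make oocyte quality rates the central mechanism: the stated purpose is live birth, and the Background speaks of numbers of follicles and mature oocytes.

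What the reply does not remove is the rule itself. The article does not leave the method for secondary rates open. It states one, and that method is unsuitable for two of the listed rates. The comment is on what is stated, not on detail left out.

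**Conclusion.** The point holds in a limited form. As written, the Pearson rule extends to two rates for which it is valid only if oocytes of one woman are independent. If it is applied to them and the within-woman correlation is positive, the comparison is too liberal: roughly 8% to 19% true type I error at nominal 5% for means of 2 to 4 oocytes and ICC 0.1 to 0.3. These inputs are assumed, and the error would be higher with overdispersed counts. At ICC 0, or if the rates are calculated per woman and tested by Wilcoxon, there is no inflation. Only these two secondary outcomes are concerned. The point should be corrected before analysis, but it does not threaten the trial's main conclusion.

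**What to change.** In the Data analysis plan, restrict the Pearson test to outcomes with one result per woman, such as pregnancy and OHSS. State that the mature oocyte and normal fertilization rates are analysed with the woman as the unit, with their denominators defined, by one of two routes:

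- a proportion for each woman, compared by the Wilcoxon test already in the plan; or
- a binomial GEE with robust standard errors clustered on woman, which also supplies the promised point estimate and 95% interval.

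Also report the numbers of mature and of normally fertilized oocytes per randomised woman, counting zero where no retrieval took place. A proportion is undefined for a woman with no oocytes, and the counts keep her in the comparison.

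The cost is a change of wording and standard software, with no new data and no change to trial conduct. Intervals will be wider than from pooled oocytes, by √DE, or about 1.10 to 1.48 times over the assumed range (√1.2 to √2.2).
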